#### Training Clinicians for the Adapted HIV+HCC Program

We conducted a clinical training for gynaecologists and nurses who will treat WLWH who have hrHPV results. Clinicians were trained in performing cervical biopsies for documentation of histological grade of disease and conducting thermal ablation and LEEP. Trainees also worked through case presentations to assist with decision making during colposcopy and treatment.

Clinicians completed pre- and post-training surveys to assess skill improvement.

#### Training GeneXperts and Pathologists

Our study addresses critical diagnostic challenges related to p-16 testing, a key marker for HPV-associated cervical dysplasia. Our pathology team, with two Nigerians and one American pathologist, identified significant gaps in their ability to perform p-16 testing due to lack of essential supplies, such as the P-16 primary antibody and detection kits. Nigerian pathologists also do not have access to digital microscopes, which are crucial for remote consultations and quality control. To address these limitations, the study procured digital smartphone microscope adaptors, which will enhance diagnostic accuracy and facilitate second reviews by pathologists for quality assurance.

As part of our efforts to standardize diagnostic procedures, we convened a meeting with Nigerian pathologists, virologists, and an Emory pathologist to review the study schema, particularly the 4-quadrant biopsy collection process. This review was essential to ensure consistent collection techniques and reliable diagnostic outcomes. We also examined the indications for p-16 staining, ensuring it is appropriately applied to cases where HPV-related dysplasia is suspected, organized training on the use of GeneXpert for HPV testing and collaboratively worked on the distribution of HPV testing cartridges and transport medium. Furthermore, we standardized terminology used on treatment evaluation forms for vaginal biopsies, ensuring that all sites are aligned in documenting biopsy results and treatment evaluations accurately.

We established quarterly quality assurance conferences to maintain diagnostic consistency, especially in the interpretation of various levels of dysplasia. Our discussions with the virologists also focused on refining protocols for sample collection, storage, shipping, and necessary reagents to ensure sample integrity. These coordinated efforts aim to enhance local diagnostic capacity while adhering to rigorous quality control standards.

#### Recruitment of WLWH

We will recruit 1500 consenting WLWH from 15 healthcare facilities (100 per facility) across eight states over a period of 18 months. A sampling frame of WLWH will be generated using a report run by the clinic staff of eligible women currently receiving care. Eligible WLWH will be contacted via telephone by the MM who will provide information about the study process. WLWH who are interested in participating will be invited to a community education meeting. Upon arrival at the community meeting, the MM will educate about HPV screening, enroll interested participants into the study and facilitate logistics for the self-screening process in a private location at the meeting site.

Eligibility inclusion criteria include:Female genderDiagnosed with HIV and receiving care at study clinicAges 25–50yAble to consent to the study

The decision to screen WLHIV age 25–50 years is based on WHO recommendation which recommends HPV screening from age 25 years up to 65 years when there are tools to manage such women. However, we chose to limit our screening to upper age of 50 years because neither VIA nor ablative treatment, which are our proposed triaging test and first line treatments respectively, are suitable for women in whom the transformation zone is not visible which is typical after menopause. WLWH will not be eligible if they are pregnant, have had a hysterectomy or are not able/willing to perform vaginal self-collection.

A sample size of 1500 WLWH was determined after considering a design effect of 1.2 (to adjust for cluster sampling) and then incorporating a dropout rate of 20%. A sample size of 1500 has 89% power to detect an absolute difference in proportions of 0.04 using a two -sided exact test with a significance level of 0.05. This calculation assumes that the population proportion under the null hypothesis (P0) is 0.79. This is based on previous research that identified the proportion of women that are willing to screen for CC [33, 34].

Each week, MMs will call eligible patients and invite them to a culturally appropriate education session on HPV screening and SC. The MM will also introduce the CHESS study and take names for women who are interested in enrolling.

The Site Coordinator will receive the list of interested women from the MM and, given resource limitations, will use a random number generator to select 10 women/month. The MM will contact the selected participants and arrange to meet them in the community, where they will consent and enroll the WLWH. Women not randomly selected will be offered alternative screening through standard of care (VIA). Upon enrollment, the participant will self-collect an HPV sample in a private space using the Evalyn Brush [32], aided by pictorial brochures and videos developed in English and the three most common Nigerian languages. MMs will transport the labelled samples securely to a laboratory for testing. The Evalyn Brush, whose accuracy is similar to clinician-collected samples [35] may be stored dry in the container it comes in at room temperature and remains stable up to 6 months. If a private collection space is not available, the MM and participant will make a plan for the return of the sample within 10 days of collection. HPV testing will be done on aliquots of samples using GeneXpert HPV platform to determine sample HPV positivity and intervention decisions. Laboratory processing of cervicovaginal samples entails pipetting 1 mL of each HPV sample into the GeneXpert HPV cartridge and then slotting the cartridge into the GeneXpert machine for processing.

The MM will be responsible for returning test results to participants. For results indicating no presence of hrHPV, the MM will counsel the participant on the meaning of the results and encourage her to retest in 3 years. For results indicating the presence of hrHPV, the MM will work with the nurse at her clinic to facilitate further evaluation and treatment by a gynaecologist.

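### The only powered test sets a willingness-to-screen benchmark of 0.79 against women for whom willingness is an entry condition, and its outcome and denominator are not fixed

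*Protocol article*

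**What the plan says.** All of this stands in the protocol article, mostly under Recruitment of WLWH.

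- **Sample:** "We will recruit 1500 consenting WLWH from 15 healthcare facilities (100 per facility) across eight states over a period of 18 months".
- **Power:** "A sample size of 1500 has 89% power to detect an absolute difference in proportions of 0.04", by a two-sided exact test at the 0.05 level. The size allows for a design effect of 1.2, "then incorporating a dropout rate of 20" per cent.
- **Benchmark:** "This calculation assumes that the population proportion under the null hypothesis (P0) is 0.79", and "This is based on previous research that identified the proportion of women that are willing to screen for CC".
- **Exclusion:** "WLWH will not be eligible if they are pregnant, have had a hysterectomy or are not able/willing to perform vaginal self-collection".
- **Route into the sample:** Mentor Mothers (MMs) telephone eligible women and list those who are interested. The Site Coordinator draws names at random from that list. Women not drawn are offered standard-of-care VIA.
- **Collection:** "Upon enrollment, the participant will self-collect an HPV sample in a private space using the Evalyn Brush". Where no private space is available, return within 10 days is arranged.

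Table 1 defines the sample-return proportion over women who had direct contact with an MM, not over enrolled women. It defines reach over all women aged 25–50 who could have been reached. The other stated quantitative analysis (Evaluation Using RE-AIM) is descriptive, with chi-squared comparisons across states.

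**The concern.** The benchmark of 0.79 is the share of women willing to be screened in a population not selected for willingness. The 1,500 women set against it have expressed interest, consented and passed an exclusion for unwillingness, and they normally give the sample at the enrolment visit. Numerator and benchmark therefore describe different populations.

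The paragraph does not say which proportion is tested or over whom. The choice matters: one reading makes success close to assured, and the other makes the stated N and the random draw unsuitable for the test. At stake is whether the one powered result could be reported as evidence that the program raised screening uptake when selection at entry would explain it.

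**Working it through.** **1. Reproduce the stated power.** Inputs from Recruitment of WLWH: N = 1,500, design effect 1.2, dropout 20%, P0 = 0.79, difference 0.04, two-sided exact test, alpha 0.05.

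- Effective n = 1,500 × (1 − 0.20) / 1.2 = 1,000.
- Exact binomial with at most 0.025 in each tail: reject upward at 816 or more of 1,000 (0.816).
- Power at 0.83 = 0.888, matching the stated 89%. At 0.75, the other side of the two-sided alternative, it is 0.838.

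The arithmetic is sound, and it shows that the 20% was taken out of n.

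**2. Reading A: sample return among the 1,500 enrolled women.** Chance of rejecting upward (816 or more of 1,000), by true return among enrolled women:

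| True return | P(reject upward) |
|---|---|
| 0.79 | 0.023 |
| 0.83 | 0.888 |
| 0.85 | 0.9985 |
| 0.90 | about 1.000 |

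The article gives no return rate for enrolled women. As an illustration with assumed values, let 30% to 79% of contacted women be willing and 90% to 98% of enrolled women return a sample. Uptake among contacted women is then between 0.30 × 0.90 = 0.27 and 0.79 × 0.98 = 0.774. The enrolled-only test succeeds with probability about 1.000 throughout. The same test at n = 1,000 on contacted women succeeds with probability below 0.001 throughout.

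**3. Reading B: sample return over women in direct MM contact (Table 1), with the telephone call counted as contact.**

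- The denominator is the number contacted, which the article does not give, so 1,500 is not the test's N.
- Interested women who are not drawn count as non-returners, although the study never offered them self-collection.
- Even if all 1,500 enrolled women return a sample, 1,500 / 0.79 = 1,898.7. The proportion is below 0.79 from 1,899 contacts upward, or 1,899 / 1,500 = 1.27 contacts per enrolled woman.

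**4. The dropout allowance.** The article does not define dropout. Suppose, as an assumption, that it meant giving no sample. Then 300 of 1,500 are affected.

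- Counted as not screened: 1,200 / 1,500 = 0.80. This does not reject, since the critical value is 1,217 / 1,500 = 0.811, or 1,016 / 1,250 = 0.813 after the design effect.
- Removed: 1,200 / 1,200 = 1.00, which rejects.

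This is a separate scenario from the high return rates in step 2; the two cannot both hold. It shows only that the handling rule can decide the result and must be stated.

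**The case against.** The strongest case on the other side has four parts.

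- **The tested outcome is inferred.** This stands. The figure 0.79 appears only in the sample-size paragraph, and the exact test may be specified in an analysis plan that is not shown. But the inference is the natural one: the benchmark concerns willingness to screen, and Aim 2 lists uptake of screening as a key outcome. No analysis plan can restore women whom eligibility and recruitment have removed.
- **Table 1 uses a wider denominator.** This also stands, and on it success is not built in. It does not rescue the power statement, because the N and the random draw then do not fit the test (step 3).
- **A reader might infer that the study says nothing about uptake.** The documents do not support that. Table 1's reach and sample-return measures describe uptake beyond the enrolled women.
- **A reader might also infer that near-complete return is certain, or that the 20% means women who give no sample.** Neither is stated. Return within 10 days leaves room for losses. The allowance may be general attrition, since treated women repeat the self-test at 1 and 2 years (Clinical Follow Up and End Points).

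**Conclusion.** The concern holds for the powered test, not for the study as a whole. The 89% is computed correctly, but for a contrast that neither available denominator supports. Among enrolled women, a result above 0.79 is close to assured once true return reaches 0.85 (probability 0.9985), and it cannot show that the program raised uptake. Over telephone contacts, 1,500 is not the sample size, and the random draw lowers the proportion for reasons unrelated to uptake.

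This rests on two assumptions: that the tested proportion is sample return, and, for the second reading, that a telephone call counts as direct contact. That the test must succeed under any reading is not supported. Even with a matching denominator, a single-arm comparison with an outside figure would not by itself attribute the result to the MMs.

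**What to change.** 1. Do not test the proportion among the 1,500 enrolled women against 0.79. Report it with a confidence interval as a process figure.
2. Define uptake as samples returned over eligible women invited by the MM, taken from the sampling frame and MM logs. Count decliners, the unwilling and non-returners as not screened. For this measure, unwillingness to self-collect must not remove a woman from the denominator.
3. Report separately the interested women who were not drawn. Deleting them while keeping every decliner would bias uptake downward. Because the draw is random, the share of invited women who are interested, multiplied by the share of drawn women who return a sample, avoids that bias.
4. Do not remove non-returners from this endpoint as dropout. Keep the 20% allowance for follow-up outcomes only.
5. Restate the sample-size justification as precision or power for that denominator, with a benchmark from a matching population, or withdraw the 89% claim for uptake. Precision is adequate: enrolling 1,500 means inviting at least 1,500. For a simple proportion with the plan's design effect, the 95% half-width is therefore at most 1.96 × √(1.2 × 0.25 / 1,500) = 0.028.
6. State in Table 1 whether a telephone call counts as direct contact.

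Enrolment stays at 1,500 and 100 per site, and the random draw need not move. The cost is protocol wording, logging of declines by the MMs, and a less favourable uptake figure. Study Aims reports that a soft roll-out has begun, so logging should start promptly.

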#### Development of Data Management Systems and Tools

Study data will be managed in REDCap. Access to the password-protected database will be restricted to approved study team members. Data will be stored on institutionally certified, password-protected, and encrypted tablets, laptops, and external drives. Only approved study staff will receive data via secure file transfer platforms.

The study team collaboratively designed Case Report Forms (CRFs) for easy completion and data entry. Questions were tailored to support analysis and quality control. MMs will complete CRFs at various CHESS study stages, and clinical personnel will complete during or immediately after exams. All CRFs will be submitted to clinic-based data clerks within 48 h. Electronic data entry screens will replicate the CRFs. Site clinicians and data managers were trained in CRF completion and REDCap data entry during a virtual pre-study session with refreshers offered. Missing or anomalous data will be sent back to sites for clarification or resolution.

#### Evaluation Using Reach, Effectiveness, Adoption, Implementation, and Maintenance (RE-AIM)

RE-AIM is a framework for planning and evaluating that assesses 5 dimensions: reach, efficacy, adoption, implementation, and maintenance [29, 30]. These dimensions occur at multiple levels including individual, clinic or organization and community and interact to determine health impact of the program. As shown in Table 1, we address relevant RE-AIM constructs for the study sample overall and by state.

Guided by the RE-AIM framework, we will use a convergent mixed-methods approach to implement a six-month, post-implementation assessment of reach, adoption, implementation, and fidelity. Quantitative and qualitive data will be collected in parallel and analyzed separately, then integrated during interpretation. Quantitative measures include numbers of women contacted, screened, and treated, numbers of MMs trained, and numbers of clinics that reach the optimal ratio (1:50) of MMs to WLWH. We chose this ratio on data from clinics in the six participating Nigerian states with input from experts in the field. The 1:50 ratio balances the needs of WLWH and the resource constraints faced by clinics/MM programs providing care. Data sources include site observations, clinical records, reports, training logs, and sample analysis. Quantitative outcome measures and data such as socio demographic/socioeconomic characteristics of participants will be analyzed using descriptive statistics and compared across states using the chi-squared test at the 5% level of significance.

To measure system flow, we will conduct rapid ethnography at a subset of 6 clinics (one per state) to assess daily clinical processes, recording observations in field notes. We will also follow 80 WLWH (10 per clinic) through the process, timing each step and noting barriers. Additionally, we will conduct virtual in-depth interviews (IDIs) with a clinical champion at each clinic (n = 15) and two focus groups (total n = 10–12) with HIV+HCC MMs to identify implementation barriers and facilitators. We will focus on MMs, who understand both systemic issues and the individual experiences of WLWH. Clinic champions will be asked to gather input from other staff before the IDIs to inform responses. Stakeholders will be informed they will participate in follow-up qualitative data collection at 18 months (Aim 3). IDIs and focus groups will be audio-recorded and transcribed, with a team member taking notes. Preliminary thematic analysis will be conducted to identify key barriers and facilitators to inform project adjustments.

Finally, we will capture project costs of adding the HCC components into the MoMent program as considerations for maintenance and sustainability. Measures will include costs for labor (clinical and laboratory staff and MMs), training and education, and clinical materials and supplies related to screening (e.g., Evalyn brush, GeneXpert Cartridge) and diagnosis (VIA consumables). Integrated findings will inform program refinement and support recommendations for scale-up and sustainability.

Aim 3Conduct post-implementation process evaluation of barriers and enablers to program maintenance.

In the maintenance phase, we will evaluate how the intervention has become routine practice at 18 months post-implementation. We will again collect data from the same stakeholders identified for Aim 2. Stakeholders’ viewpoints and processes related to the RE-AIM construct of “maintenance” will be assessed via quantitative measures (Table 1), structured interviews (n = 15), focus groups (n = 10–12), and numbers of WLWH screened/treated during the maintenance period. Stakeholders will also identify barriers to maintenance, resources available to support and capacity to scale the intervention across Nigeria.

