#### Site Selection

Fifteen PEPFAR-supported clinics across 8 Nigerian states were selected based on geographic diversity (including urbanicity), level of care, ownership, and patient volume, to represent the diversity of care settings in Nigeria. Each site aims to recruit 100 WLWH aged 25–50.

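### The chi-squared comparison across states treats women as independent although the study was sized for clustering by clinic; at the plan's own design effect its true error rate is about 11%, not 5%.

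*Protocol article*

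**What the plan says.** Three places in the protocol article bear on this.

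- **Evaluation Using RE-AIM.** Quantitative outcomes and participants' sociodemographic data are to be summarised descriptively and "compared across states using the chi-squared test at the 5% level of significance". No adjustment for clinic is mentioned. This is the only test the article names for analysing these data.
- **Recruitment of WLWH.** The sample size was set "after considering a design effect of 1.2 (to adjust for cluster sampling"), and then for 20% dropout. The article states that "A sample size of 1500 has 89% power to detect an absolute difference in proportions of 0.04", using a two-sided "exact test with a significance level of 0.05", with a null proportion of 0.79. Recruitment is 100 women at each of 15 facilities in eight states. No ICC is given.
- **Site Selection.** The clinics were chosen for variety in location, level of care, ownership and volume, "to represent the diversity of care settings in Nigeria".

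Table 1 presents its measures in total and by state. Some rows count women, others count clinics or Mentor Mothers.

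**The concern.** The design section and the analysis section make different assumptions about the same women. The first expects women from one clinic to resemble each other. The second names a test that is valid only if they do not.

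The layout makes this worse. Two clinics in each of eight states would need 16 clinics, and there are 15, so at least one state has a single clinic. There, a state difference and a clinic difference are the same thing. In the other states, about two clinics carry all the information about the state.

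At stake is how differences between states are read. Ordinary variation between clinics would be reported as a state effect more often than the stated 5%. The six-month results are meant to inform programme refinement and recommendations for scale-up.

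**Working it through.** **Inputs from the document:** 1,500 women; 15 clinics of 100; eight states; dropout 20%; design effect (DE) 1.2; null proportion 0.79; difference 0.04; two-sided 5% level.

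**Assumptions:** dropout is spread evenly, leaving 80 women per clinic and 1,200 in all. Clinics act as sampled clusters. The DE of 1.2, given for the screening proportion, also holds for the outcome being compared. The split of clinics over states is not given, so two were tried: seven states with two clinics and one with one; and 4-3-2-2-1-1-1-1.

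**1. The plan's own figure.** Effective n = 1,500 × 0.80 / 1.2 = 1,000. The exact two-sided binomial test of 0.79 against 0.83 then has power 0.888, which agrees with the stated 89%. Without the design effect, power would be 0.941 at n = 1,200 or 0.974 at n = 1,500. The stated power therefore already allows for clustering.

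**2. ICC implied by 1.2.** ICC = (DE − 1)/(m − 1):
- m = 100: 0.2/99 = 0.0020
- m = 80: 0.2/79 = 0.0025

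The between-clinic standard deviation is √(ICC × 0.79 × 0.21), or 1.8 to 2.0 percentage points.

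**3. True size of the state chi-squared at DE 1.2.** Eight states give 7 df and a 5% critical value of 14.07. Under clustering the statistic is inflated by about the DE, so the true size is P(χ²₇ > 14.07/1.2) = P(χ²₇ > 11.72) = 0.110. A beta-binomial simulation (20,000 runs, 80 per clinic) gave 0.106 to 0.110 over the two layouts. With no clustering it gave 0.049, so the excess comes from clustering and not from the approximation.

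**4. Sensitivity to the ICC.** These ICCs are assumed, with m = 80 and DE = 1 + 79 × ICC.

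| ICC | DE | Size of state chi-squared (simulated, seven states with two clinics, one with one) |
|---|---|---|
| 0.0025 (the plan's 1.2) | 1.20 | 11% |
| 0.01 | 1.79 | 35% |
| 0.02 | 2.58 | 60–61% |
| 0.05 | 4.95 | 90% |

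**5. Number of states.** The RE-AIM section also speaks of six states. With six, the test has 5 df and a critical value of 11.07; 11.07/1.2 = 9.23 and P(χ²₅ > 9.23) = 0.100. The conclusion is unchanged, although a state with a single clinic is then no longer forced.

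**6. The overall proportion.** If the exact test were run unadjusted on 1,200 women, its size at DE 1.2 would be about 2 × P(Z > 1.96/√1.2) = 0.074 (simulated 0.074).

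**7. Rows that count clinics or Mentor Mothers.** 15/8 = 1.9 clinics and 30/8 = 3.75 Mentor Mothers per state on average. Expected cell counts are below 5 even before splitting by outcome, so a chi-squared approximation is unreliable in any such row.

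**8. Does a remedy hold its level?** A clinic-level F test of state (8 − 1 = 7 and 15 − 8 = 7 df) had simulated size between 4.9% and 5.5% over both layouts and all the ICCs above.

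**The case against.** The strongest reply is that the 15 clinics were selected and not drawn at random. If the question is only whether these particular clinics, grouped by state, differ, clinic effects are fixed. With fixed differences of 2 to 6 points within states and equal state averages, the simulated chi-squared size was 4.6% to 5.0%. That is right as far as it goes. However, the sample-size paragraph itself treats clinics as sampled clusters, and the sites were chosen to stand for care settings in Nigeria. A conclusion confined to these clinics would describe clinics, not states.

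Other parts of the reply stand and limit the point:

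- A reader might infer that the exact test also ignores clustering. The document does not support that. The test appears only in the sample-size sentence, its power was computed after the design effect, and the analysis of the overall proportion may be set out in a plan that is not shown.
- A reader might infer that the 89% power is wrong because an ICC of 0.002 is too small. Nothing in the document shows this. Choosing varied clinics suggests heterogeneity but does not size it, so higher ICCs are sensitivity values only.
- The article does not say which Table 1 rows will be tested, so the remark on clinic-level and Mentor Mother-level rows applies only if they are.
- The state comparison belongs to a largely descriptive evaluation, and no decision rule depends on it.

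**Conclusion.** The point holds for the state comparison. As written, a nominal 5% chi-squared test across eight states has a true size of about 11% under the plan's own design effect, and more if clinics vary more than 1.2 implies. The 11% rests on treating clinics as sampled clusters and on carrying the 1.2 over to the outcomes compared. It does not depend on which of the two clinic layouts is used. The sizes of 35% to 90% rest on assumed ICCs and are not evidence of an error in the document.

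The stated power is correct at a design effect of 1.2. For the overall proportion there is only a conditional risk: a size of about 7% if the adjustment used in sizing is dropped at analysis. This should be fixed, but it does not threaten the study's main conclusions.

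**What to change.** 1. Replace the ordinary chi-squared across states with a test that accounts for clinic and has a small-sample correction: a clinic-level or design-based F test with 7 and 7 df for eight states, or a Rao-Scott test with an F reference. Alternatively, drop the test and report state differences descriptively with cluster-adjusted intervals. Settle the number of states first; six would give 5 and 9 df.
2. Do not rely on a mixed logistic model with a clinic random intercept and no small-sample correction. A Gaussian approximation to its likelihood-ratio test had size 7% at design effect 1.2, and 17%, 24% and 28% at ICCs of 0.01, 0.02 and 0.05.
3. Report any clinic-level and Mentor Mother-level rows by state descriptively only.
4. State that the overall proportion will be analysed with the cluster adjustment used to size it.
5. Optionally, state the implied ICC of 0.002 to 0.0025 and show power over a range.

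The cost is analysis wording; recruitment and conduct do not change. The downside is wider intervals and a weak state comparison. At design effect 1.2 the F test had simulated power of only about 19% to 23% when true state proportions were spread evenly from 0.73 to 0.85. That is a reason to prefer the descriptive option.
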